##### Sensitivity Analyses

To determine the reliability of the analyses for research questions 1 and 2, we will conduct sensitivity analyses for our primary and secondary outcomes. We will include only complete cases (complete data for T0, T1_,_ T2, and T3).

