## Methods

### Design

We will conduct a multicenter RCT with a WCG design using individual-level randomization, stratified by the hospital or nursing school. The WCG will receive the digitally supported mindfulness intervention 14 weeks after allocation.

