#### Participant Timeline

The study will be conducted over a 10-month period (Table 1). A total of 4 surveys will be conducted 3 months apart from one another. Participants will be allowed 2.5 weeks to complete each survey. All participants randomized to the IG will receive access to the digitally supported mindfulness intervention 2 weeks after T0 data collection. All participants randomized to the WCG will receive access to the digitally supported mindfulness intervention 2 weeks after time point 1 [T1] data collection (14 weeks after the IG has been given access). Data collection for both groups will take place at 10, 24, and 38 weeks after allocation. In other words, data collection for each group will take place at 10 weeks (T1 for the IG and time point 2 [T2] for the WCG) and 24 weeks (T2 for the IG and time point 3 [T3] for the WCG) after intervention start. For individuals randomized to the IG, data will be collected at 38 weeks after the intervention starts (T3).

**Table 1 table1:** Schedule of enrollment, interventions, and assessments for the intervention group (IG) and the wait-list control group (WCG).

		Enrollment	Baseline	Random allocation	After allocation			
			T0^a^	Intervention start IG	T1^b^	Intervention Start WCG^c^	T2^d^	T3^e^

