#### Statistical Methods

##### Overview

Analyses will be conducted using *SPSS Statistics* (IBM)*.* For tests involving our primary outcome variable, we will set an α level of .05. For all other analyses, to reduce α-error inflation, we will interpret the obtained *P* values descriptively, meaning all other analyses will be exploratory and are designed to observe trends and not to identify significance.

Patterns of missing data will be assessed, and adequate data imputation techniques such as multiple imputation with *SPSS Statistics* (IBM) will be applied. Before doing so, we will assess the percentage of missing data. We will also use Little's Missing Completely At Random test to determine patterns of missing data (ie, missing completely at random vs not missing at random).

We will reverse code 3 outcomes [32,38,40] so that a higher score indicates health improvement. For example, the scale assessing burnout [40] is designed to indicate that a score of 1 indicates a rather minuscule risk of burnout, whereas a score of 100 indicates the highest risk of burnout, meaning that greater scores indicate a worsening of symptoms. After recoding this variable, greater scores will reflect a lower risk of burnout (ie, an improvement in symptoms).

Effectiveness will be evaluated using an intention-to-treat (ITT) approach; all randomized participants will be included in our analyses [45].

Efficacy will be evaluated using a per-protocol (PP) approach; only study completers who report adherence will be included in our analyses.

Several analyses will be used to address the research questions. To ensure that our randomization has worked as intended, we will assess for between-group differences for relevant participant characteristics and, if needed, adjust the following analyses. For research questions 2, 3, and 4, we will create a pooled data set merging the data of the IG and the WCG. We will merge the data of the 2 groups so that IG T0 data will be combined with WCG T1 data, and IG T1 data will be combined with WCG T2 data, as described in Textbox 1. For research questions 3 and 4, relationships between variables will be examined using correlation analyses (Pearson correlation coefficient, eta quotient, and chi-square tests). If violations of the assumptions associated with any of the analyses are detected, alternative tests will be used.

Data pooling procedure.

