**Newly pooled data set and data included**
Participant data baselineCases of the intervention group at time point 0Cases of the wait-list control group at time point 1Participant data 10 weeks after intervention startCases of the intervention group at time point 1Cases of the wait-list control group at time point 2Participant data 24 weeks after intervention startCases of the intervention group at time point 2Cases of the wait-list control group at time point 3

##### Research Question 1

We will present the ITT sample’s baseline characteristics and test for detectable between-group differences. For continuous variables, mean, SD, median, minimum, and maximum values will be calculated. For categorical variables, frequencies (absolute and percentages) will be calculated.

To evaluate the effectiveness and efficacy of the 10-week access, we will create one difference score per group for each of our outcomes assessed at T0 and T1. Using a 2-sample *t* test, we will test whether significant differences exist between the 2 difference scores in the IG and WCG. We will perform this for the ITT and PP sample. If *P*<.05, Cohen *d* will be calculated.

##### Research Question 2

To evaluate long-term effectiveness and efficacy, we will use the pooled data set. To analyze the effect of time on our variables of interest, a repeated-measures ANOVA will be conducted for each of our outcomes. As only participants randomized to the IG will be assessed at 38 weeks after allocation, long-term efficacy within this group will be examined using an additional repeated-measures ANOVA.

Using a PP approach, we will examine the relationship between *app-based minutes of meditation* and each previously calculated difference score using the pooled data set. Linear regression will be performed to examine the relationship between the minutes of meditation and each outcome. The baseline scores of primary and secondary outcomes will be entered into the model as additional explanatory variables to control for individual differences before the start of the intervention.

##### Research Question 3

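### The complete-case sensitivity analysis for the 10-week comparison requires surveys at weeks 24 and 38, which that comparison does not use and which follow the control group's start of the intervention

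*Protocol article*

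**What the plan says.** The Sensitivity Analyses section states its scope: "To determine the reliability of the analyses for research questions 1 and 2, we will conduct sensitivity analyses for our primary and secondary outcomes". The set is then fixed in one sentence, "We will include only complete cases (complete data for T0", and the parenthesis goes on to list T1, T2 and T3. No separate set is given for each research question.

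Under Research Question 1 the analysis needs two waves: "we will create one difference score per group for each of our outcomes assessed at T0 and T1". The test is "Using a 2-sample *t* test, we will test whether significant differences exist between the 2 difference scores in the IG and WCG".

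On timing, the Design section says "The WCG will receive the digitally supported mindfulness intervention 14 weeks after allocation", and Participant Timeline says "Data collection for both groups will take place at 10, 24, and 38 weeks after allocation". T1 (week 10) is thus the only follow-up survey before the wait-list control group (WCG) gets access. T2 (week 24) and T3 (week 38) both come after.

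For the main effectiveness analysis, the Statistical Methods overview says "all randomized participants will be included in our analyses", with imputation of missing data and multiple imputation named as an example. The per-protocol analysis is limited to study completers who report adherence.

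**The concern.** A complete-case analysis of the 10-week comparison is the natural companion to an imputed one, because it shows how far the result depends on the imputation. For that purpose it should contain everyone whose T0 and T1 data were observed. Under the stated rule, someone who answered both surveys is removed for missing a survey 14 or 28 weeks after the endpoint.

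This has two consequences. The set is smaller than it needs to be, in a trial that randomized 79 people against a target of 90. Membership also depends on behaviour after randomization, after the endpoint and after the control group's start. Between T1 and T3 the intervention group (IG) continues something it already has, while the WCG begins it. If people with a good or poor T1 response are kept at different rates in the two arms, the completers' contrast can differ from the contrast among all observed T0-T1 pairs. A discrepancy with the intention-to-treat result could then come from the imputation or from this later selection, and the plan could not tell which.

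**Working it through.** **Waves used and waves required**

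| Analysis | Waves it uses | Waves the rule requires |
|---|---|---|
| Research question 1, IG v WCG | T0, T1 | T0, T1, T2, T3 |
| Research question 2, pooled set, IG members | T0, T1, T2 | T0, T1, T2, T3 |
| Research question 2, pooled set, WCG members | T1, T2, T3 | T0, T1, T2, T3 |
| Research question 2, IG-only 38-week analysis | T0 to T3 | T0 to T3 |

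The rule matches only the last row.

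**Access at the later waves.** The IG starts at allocation and the WCG at week 14.

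- T2: IG 24 weeks; WCG 24 − 14 = 10 weeks.
- T3: IG 38 weeks; WCG 38 − 14 = 24 weeks.

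**The plan's own figure.** Inputs from Sample Size: d = 0.67, two-sided alpha 0.05, power 0.80, equal groups, 20% dropout. Power comes from the noncentral t distribution with noncentrality d × √(n₁n₂/(n₁+n₂)) and n₁+n₂−2 degrees of freedom. At 36 per group the noncentrality is 0.67 × √18 = 2.843 and power is 0.8005; at 35 per group it is 0.789. So 36 per group (72) reproduces, and 36/0.8 = 45 per group (90) reproduces.

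**Size of the loss.** The protocol gives no attrition by wave, so the per-wave rates are assumptions. With 79 randomized (40 IG, 39 WCG; Results) and loss at rate r per wave, T0-T1 pairs = 79(1−r) and four-wave completers = 79(1−r)³.

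| Assumed loss per wave | T0-T1 pairs | Four-wave completers | Cumulative loss | Power at d = 0.67 |
|---|---|---|---|---|
| 10% | 79 × 0.9 = 71.1 | 79 × 0.729 = 57.6 | 27.1% | 0.795 (36 v 35) to 0.708 (29 v 29) |
| 20% | 79 × 0.8 = 63.2 | 79 × 0.512 = 40.4 | 48.8% | 0.744 (32 v 31) to 0.542 (20 v 20) |

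The Introduction cites dropout of about 25% to 48% in similar studies. The first row lies near the bottom of that range and the second just above its top. In between, 20% loss by T1 with 30% or 40% missing any wave by T3 gives 63 pairs against about 55 or 47 completers (power 0.69 or 0.62). If nobody with T0 and T1 misses T2 or T3, nothing is discarded.

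**When the rule biases the check.** This simulation is illustrative, and all its inputs are assumed: change scores with SD 1, about 65% to 70% kept after T1, and the log-odds of being kept rising or falling by 0.5 per SD of T1 improvement.

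| Link between T1 improvement and later retention | Completers' estimate, true effect 0 | Completers' estimate, true effect 0.67 |
|---|---|---|
| None in either arm | 0.00 | 0.67 |
| Positive in IG, none in WCG | 0.17 | 0.81 |
| Positive in IG, negative in WCG | 0.34 | 0.98 |
| Positive and equal in both | 0.00 | 0.64 |

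The contrast among all T0-T1 pairs returned the true value in every row.

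**The case against.** Four points on the other side have force.

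- **The main result is untouched.** The primary analysis includes all randomized participants with imputation. Only a robustness check is affected. This stands.
- **The bias is conditional.** A reader might infer that the rule breaks the randomized comparison or makes the check worthless. The documents do not support that. Bias under no effect needs a link between T1 change and later retention that differs by arm, and nothing in the protocol shows one. A reader might also suppose that the WCG has only just started when retention is judged. It has had 10 weeks of access at T2 and 24 at T3, so the arms differ in exposure, but less starkly than that.
- **Power is a secondary yardstick.** A sensitivity analysis asks whether the estimate is stable and is not sized to reject. The figures above show how much information is discarded, and the 20% row is close to a worst case. The shortfall of 79 against 90 has nothing to do with this rule. A T0-T1 complete-case set also conditions on response after randomization, at T1, so it is less exposed but not free of the problem.
- **A single four-wave cohort has a rationale.** It keeps the same people in view across both questions, and the IG-only 38-week analysis does need T3. That does not justify imposing T2 and T3 on a T0-T1 comparison.

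The per-protocol analysis, which the limitations section offers together with intention-to-treat as protection against loss to follow-up, does not fill the gap, because it is restricted to adherent completers. The article gives no imputation analysis under departures from missing at random, but that is a detail a separate analysis plan may hold, and its absence is not counted here.

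**Conclusion.** The point holds as a mismatch between a stated rule and the analysis it is meant to check. The four-wave requirement can only remove valid T0-T1 pairs from the check on the 10-week comparison: about 13 of 71 at an assumed 10% loss per wave (71 − 58), and about 23 of 63 at 20% (63 − 40). The counts rest on assumed attrition, equal in both arms and at every wave.

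Whether the check is also biased cannot be determined from the document, nor can direction or size. Under the assumed arm-specific links the shift with no true effect was 0.17 to 0.34 SD. With no link, or an equal link in both arms, it was zero. The defensible statement is that the rule costs precision and may bias the check. It should be corrected because it is the only labelled sensitivity analysis for the primary outcome and the correction is nearly free. The primary intention-to-treat conclusion does not depend on it.

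**What to change.** Replace the single rule with one set per analysis:

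- Research question 1: complete cases are participants with T0 and T1 present.
- Research question 2, pooled data set: T0, T1 and T2 for IG members; T1, T2 and T3 for WCG members.
- Research question 2, IG-only 38-week analysis: T0 to T3, as now.

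Report the number in each set by arm beside the number randomized. If a common cohort is wanted for comparing the two questions, the four-wave set can be kept as an extra, labelled as such. An imputation analysis that worsens imputed T1 values in steps would be a useful option, but this correction does not require it.

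The cost is a wording change, with no new data. The one drawback is that the sensitivity sets for research questions 1 and 2 will no longer be the same people, which the report should state.

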### Ethical Considerations

#### Research Ethics Approval and Amendments

The IRB approved this study in July 2021 (S-53/2021). If and when applicable, amendments will be submitted to the IRB. After the study is completed, all nurses employed at the study sites will be given free 12-month access to the intervention.

#### Confidentiality and Access to Data

Personal information about potential and enrolled participants will be collected only by members of the research team and cannot be accessed by other individuals. Personal information and survey data will be pseudonymized using an identification number (token). Only authorized study personnel will have access to any of the data associated with this study. The study funder reserves the right to share the anonymized data with other parties.

## Results

Data collection at T0 was conducted from the end of September 2021 until October 2021. At the end of October 2021, a total of 79 individuals were randomized to either the IG (40/79, 51%) or WCG (39/79, 49%). All data collection will be completed by the beginning of August 2022. Data analyses will begin after data collection and will be completed by December 2022.

## Discussion

Mixed results have been found for digitally supported mindfulness interventions for nurses working in acute inpatient care settings [16,20-23], highlighting the need for planned research involving long-term follow-ups and analyses of factors of adherence and acceptability-related variables.

### Expected Results

Our study design, involving long-term follow-up, a standardized intervention, and our planned investigation variables related to adherence and acceptability, will allow us to rigorously evaluate the effectiveness and efficacy of a digitally supported mindfulness intervention among nurses and nursing trainees working in acute inpatient care settings. The findings of our study will provide valuable information regarding the design and implementation of future stress management interventions for nurses and nursing trainees in acute inpatient care settings.

On the one hand, the digital nature of this intervention allows for the accommodation of nurses’ busy work schedules, thus increasing the likelihood of ongoing meditation practice and resulting in higher effectiveness. Given their user-engaging design, the workbook and web-based workshop components may further contribute to the participants’ maintained interest in digitally supported mindfulness intervention use. On the other hand, previous research has revealed that implementing health promotion efforts into a demanding daily work routine presents a challenge for nurses worldwide [46], and the unpredictable nature of COVID-19–related conditions likely exacerbates the challenge to implement new stress management habits.

### Comparison With Prior Work

For comparison with other studies, we will consider the method and context of the study. These include COVID-19–related working conditions, country, definition of ITT and PP, duration of the intervention, and previously identified variables related to adherence and acceptability.

### Generalizability

Results regarding effectiveness, efficacy, adherence, and acceptability may be generalizable to other health care professionals working in similar settings and nurses working in different care settings, as the app contains not only contents specifically tailored to nurses working in German inpatient care settings but also a variety of meditations and courses on various mindfulness topics (>900) independent of any specific context. By conducting a multicenter study, the generalizability may be further improved.

The generalizability of our results may be limited as COVID-19–related health care burden and hospitalization rates vary widely across countries and continents; stressors experienced by nurses and nursing trainees working in Germany may differ from stressors experienced by nurses working in other countries. In addition, nursing training requirements may differ across countries; for example, nursing trainees in Germany are required to gain hands-on work experience from the start of their training [47]. By receiving reminders to participate in the web-based surveys, participants are likely inadvertently reminded to interact with the app. As these reminders do not occur in real-world settings, the applicability of the findings from our RCT and others should be interpreted with caution.

### Strengths and Limitations

The study results will be reported in accordance with international documentation guidelines, including CONSORT-EHEALTH (Consolidated Standards of Reporting Trials of Electronic and Mobile Health Applications and Online Telehealth) statements [48,49] (Multimedia Appendix 2). We anticipate that our study will have high validity and reliability. In addition, an RCT allows for the identification of the causal effects of our intervention.

Our study will not include an active control group, which is a common limitation in similar studies. The study design was chosen as the primary aim of the study is to evaluate the intervention relative to no intervention, and WCGs are an ethical option to provide the intervention quickly to all participants [50]. A third experimental condition was discussed; however, we ultimately decided against this, given our small sample size.

Our WCG study design is associated with several limitations. This study design may overestimate intervention effects [50], as beneficial effects may occur among participants randomized to the IG simply because of the time spent away from work when participating in web-based workshops. These effects can be identified by including an active control group [10,51]. Furthermore, placebo effects and effects occurring because of participants’ expectations may occur with our study design. On the one hand, participants may experience some beneficial effects because of their anticipation of the upcoming intervention [52], which may be further increased by digitalization-specific expectations and participants’ trust in the study funder (a large health insurance company) [53]. On the other hand, previous research suggests that participants in WCGs do not improve until they receive the intervention [54].

Our study aims to investigate the effects of this intervention in its entirety. Our study design and analyses do not allow for conclusions regarding the intervention components that drive the identified effect or the proportion of the observed variance that is explained by each component. Some content commonly found in mindfulness interventions may lead to reduced stress [55]. However, several components could influence stress reduction among the participants in our study, irrespective of the mindfulness construct embedded in our intervention. First, the app contains educational content about stress management in general and features relaxation techniques such as the Jacobson progressive muscle relaxation. Second, the app prompts users to engage in self-reflection and mood monitoring and to read the educational content, which in itself can motivate the individual to engage in behavior change that may, in turn, facilitate stress reduction. Third, listening to nature sounds [56] or viewing visually appealing content may improve mood and enhance relaxation. Finally, the web-based workshops take place in group settings, and include social interaction with the trainer [15,55] and one’s peers may lead to stress reduction. However, we consider the variety of content provided to the users as a strength of the intervention, as users can choose the content most suitable and effective for them.

Selection bias because of the uneven distribution of confounders is usually not a cause for concern in large RCTs, as one can assume that latent and manifest variables are balanced equally across conditions. For smaller RCTs such as ours, there are steps that can be taken to reduce the risk of uneven distribution of latent or manifest variables across groups. To minimize the risk of confounding variables, we have used stratification for our randomization processes. Furthermore, single-blind randomization and allocation will be used to reduce selection bias. To ensure that our randomization has worked as intended, we will assess for between-group differences for relevant participant characteristics.

Detection bias may occur as blinding of participants is not possible, given the nature of the study. Although the study design is not communicated to the participants, the participants are to be likely aware of which group they have been randomized to. There may be a risk of social desirability as the effects will be evaluated based on subjective reports, including the frequency and intensity of digitally supported mindfulness intervention use, and no biological parameters will be collected. To reduce detection bias, all questions were tested among members of the target group before the start of the study, and all outcome measures were validated in previous studies. Evaluations of the psychometric properties of our primary outcome, the PSS-10, in different countries report a Cronbach α of .78 to .91, with good test-retest reliability [57]. PSS-10 scores correlate significantly with cortisol levels and constitute an objective measure of cumulative stress [58]. We will also seek to reduce the risk of social desirability by informing participants of the pseudonymization and anonymous publication of the data and by conducting data collection without in-person contact. In addition, we will not use participant data collected via the app but will allow participants to report data collected by the app. We refrained from tracking app use and the duration of use for privacy reasons. Not tracking app use may increase rapport, as participants will not feel monitored while using the app. Finally, the item with which we assessed gender may present a limitation as the German language uses the same term for sex assigned at birth and gender identity; thus, we cannot be certain whether participants reported their sex or their gender.

Performance bias will be reduced by using a standardized intervention; however, COVID-19–related differences may occur, as the WCG will receive the intervention at a later time.

Attrition bias may occur in individuals with little technical experience. By conducting a web-based survey, individuals with an affinity for technology are more likely to participate in the surveys on an ongoing basis. This restriction cannot be avoided because of pandemic-related regulations. To reduce bias through loss to follow-up (attrition bias), we will send reminder emails of survey participation, and participation in the survey will be incentivized by the intervention provider at one hospital. We will conduct ITT and PP analyses to reduce the risk of misinterpretation of results because of loss to follow-up.

